## Abstract

**Background:**

Patients who start renal replacement therapy (RRT) for End-Stage Kidney Disease (ESKD) without having had timely access to specialist renal services have poor outcomes. At one NHS Trust in England, a community-wide CKD management system has led to a decline in the incident rate of RRT and the lowest percentage of patients presenting within 90 days of starting RRT in the UK. We describe the protocol for a quality improvement project to scale up and evaluate this innovation.

**Methods:**

The intervention is based upon an off-line database that integrates laboratory results from blood samples taken in all settings stored under different identifying labels relating to the same patient. Graphs of estimated glomerular filtration rate (eGFR) over time are generated for patients <65 years with an incoming eGFR <50 ml/min/1.73 m^2^ and patients >65 years with an incoming eGFR <40 ml/min/1.73 m^2^. Graphs where kidney function is deteriorating are flagged by a laboratory scientist and details sent to the primary care doctor (GP) with a prompt that further action may be needed.

We will evaluate the impact of implementing this intervention across a large population served by a number of UK renal centres using a mixed methods approach. We are following a stepped-wedge design. The order of implementation among participating centres will be randomly allocated. Implementation will proceed with unidirectional steps from control group to intervention group until all centres are generating graphs of eGFR over time.

The primary outcome for the quantitative evaluation is the proportion of patients referred to specialist renal services within 90 days of commencing RRT, using data collected routinely by the UK Renal Registry. The qualitative evaluation will investigate facilitators and barriers to adoption and spread of the intervention. It will include: semi-structured interviews with laboratory staff, renal centre staff and service commissioners; an online survey of GPs receiving the intervention; and focus groups of primary care staff.

**Discussion:**

Late presentation to nephrology for patients with ESKD is a source of potentially avoidable harm. This protocol describes a robust quantitative and qualitative evaluation of a quality improvement intervention to reduce late presentation and improve the outcomes for patients with ESKD.

## Background

Chronic kidney disease (CKD) is a common long-term condition that affects up to 14% of adults in England [1]. All patients with CKD are at increased risk of cardiovascular disease [2], and an important minority will develop progressive renal disease. In the most severe cases (end-stage kidney disease, ESKD), treatment with kidney dialysis or transplantation (renal replacement therapy, RRT) is required to sustain life. ESKD is strongly associated with increased mortality [3]. Although survival rates on RRT have improved over the last 15 years, the relative risk of death in RRT patients in the UK in 2013 across all ages was 6.2 compared with the general population [4]. Outcomes are particularly poor in those who present to renal centres with insufficient time to prepare adequately for RRT; the risk of death in such patients is approximately doubled as compared with those referred earlier [5], as a consequence of factors including greater use of temporary vascular access and delayed referral for transplantation. Late presentation, which is a term conventionally applied in the case of patients first seen by renal services within 90 days of starting RRT, is therefore an important cause of avoidable harm. In 2013–2014, the proportion of patients presenting late varied across UK renal centres from 4.9 to 33.9%, see Fig. 1 [6]. Reducing this variation is an important target for quality improvement activities. Of note, acute kidney diseases can develop *de novo* and cause ESKD within 90 days, accounting for 28% of overall late presentation [6]. Therefore it is impossible to avoid late presentation entirely, but this should be minimal for the majority of patients with non-acute renal disease.

**Fig. 1 Fig1:**
[figure not shown]
Variation in rate of late presentation to renal services across renal centres in the UK (2013–14). Reproduced with the kind permission of the UK Renal Registry [6]

A system of graphical surveillance of kidney function over time (“eGFR graphs”) has been operating at the Heart of England Foundation Trust in people attending the diabetes service since 2004 and across the entire population served by the Trust since 2012. It is the central part of a community-wide CKD surveillance system that has been associated with a decline in the incident rate of renal replacement and the lowest percentage of patients referred late (most recently 4.9%) for dialysis in the UK [6, 7]. The eGFR graph system identifies patients who are at high risk of requiring renal replacement therapy and who otherwise may not have received timely specialist attention. It is perceived by general practitioners to be easy to use and helpful in improving patients’ management [8]. A similar service implemented in the Kaiser Permanente system in Hawaii has led to improved outcomes mirroring those reported from HEFT [9].

## Aims and objectives

The overarching aim of ASSIST-CKD is to drive large-scale, measurable and sustainable change that reduces the burden of chronic kidney disease across the UK, and in particular reduces late presentation for RRT. We propose to achieve this through the phased implementation, across locations, of routine surveillance and reporting of eGFR graphs by pathology laboratories, thereby facilitating the early recognition and timely referral in primary care of patients with deteriorating kidney function.

## Methods

### Project intervention

Graphical surveillance of all estimated glomerular filtration rate (eGFR) results analysed within a participating pathology laboratory, and the reporting in graphical form of results deteriorating over time to the requesting clinician.

A dedicated laboratory database operating on an SQL server integrates blood samples taken in all settings, i.e., community and hospital, and merges results stored under different identifying labels relating to the same patient. Graphs of eGFR over time are automatically generated for patients aged ≤65 years with eGFR <50 ml/min/1.73 m^2^ and patients >65 years with eGFR <40 ml/min/1.73 m^2^ using a dedicated software package, see Fig. 2 for examples. As eGFR results can be variable and unpredictable over time, the graphs are reviewed by a laboratory scientist or renal nurse. Graphs where the kidney function is clearly deteriorating are flagged.

**Fig. 2 Fig2:**
[figure not shown]
Examples of the graph intervention generated in the laboratory (**a**) low but stable function and (**b**) declining function (Graph 2b would generate an alert for the clinician as indicated by the red line)

The graphs from flagged patients are sent to the referring general practitioner, together with a prompt that further action, such as referral to specialist renal services, may be needed. These prompts can be adapted to meet local needs. The graphs are presented in a format that is meaningful to patients, and practitioners are encouraged to share the materials with patients to help increase their understanding of kidney disease. The laboratories are encouraged to include links to educational resources for primary care on progressive CKD with the graphs. A log of the patients on whom graphs are sent is kept.

### Education

Educational and training materials (both project-specific and generic) are available to participants. Learning events are being held at regular intervals throughout the life of the project, to bring together members of the project team and collaborators from the participating centres to share experiences and learning.

#### Laboratory staff

A pack for participating labs has been developed. This includes a role description for the laboratory staff reviewing the graphs, a Standard Operating Procedure, a User Guide, including a “YouTube” summary of how to run the software and interpret the graphs, and a summary of the IT specification. For external quality assessment, all individuals at participating sites who will be reviewing the graphs are invited to report an anonymised test set of 30 patients’ graphs supplied by the team at HEFT. The test set included graphs that are clearly progressive, stable and more nuanced. The outcome for each interpretation was agreed by consensus among consultant nephrologists and clinical scientists after independent review. Before live reporting can commence the reviewers are required to correctly flag all 10 of the subset of compulsory graphs showing clearly progressive CKD and in addition achieve a score of 80% overall.

The model used at the Heart of England Foundation Trust (HEFT) is for graphs to be reviewed by a Band 7 Clinical Scientist on the Health and Care Professions Council register. Review by a renal nurse may be possible in some locations. Oversight and supervision is provided by consultant Clinical (or Medical) Scientist. For sites where other models are proposed these will be examined on a case-by-case basis by the project team; in all cases a period of formal training and directly observed working followed by sign-off by the local consultant Clinical (or Medical) Scientist lead will be required.

#### Primary care staff

e-learning resources for primary care are freely available (http://www.ckdonline.org/ and http://www.theisn.org/education/education-topics/general-nephrology/item/2420-free-book-chapters-understanding-kidney-diseases).

#### Patients

An information booklet on CKD to inform patients and carers about what the results of an eGFR test might mean is freely available on-line and practices will be made aware of it (https://www.kidneyresearchuk.org/health-information/resources/looking-after-your-kidneys).

### Project design

It is planned that the eGFR graph intervention will be implemented in laboratories serving at least nineteen renal centres across the UK. All sites participating in this quality improvement programme will receive the intervention. However implementation will proceed in a phased stepped wedge manner (“stepped wedge cluster randomised trial”) to allow a robust outcome evaluation to be conducted. Without this design, evaluation of the overall project success may be overly optimistic due to the phenomenon of “early-adopters”.

The unit of intervention in the project is the pathology laboratory. However project outcome measures are aggregated at the level of the renal centre. Where more than one laboratory lies within the catchment of a main renal centre, where possible the intervention will be implemented in all these laboratories simultaneously.

The intervention will be rolled-out sequentially, with renal centre clusters (and their associated pathology laboratories) receiving the intervention at staggered time points. The plan is for four or five renal centres to begin implementation at each “step”, with a six-month interval between steps. The time of intervention initiation will be randomised. Crossover is unidirectional (from control to intervention) so eventually all participating centres will implement the intervention, see Table 1 for a representation of the step-wedge process.

**Table 1 Tab1:** Study period with randomisation steps

Centres	Historical control-periods				Periods of core-study					
	(4 × 6 months)				Jan-Jun	Jul-Dec	Jan-Jun	Jul-Dec	Jan-Jun	Jul-Dec
	Jan-2013 - Dec 2014				2015	2015	2016	2016	2017	2017
A – D	0	0	0	0	0	1	1	1	1	1
E – I	0	0	0	0	0	0	1	1	1	1
J – N	0	0	0	0	0	0	0	1	1	1
O – R	0	0	0	0	0	0	0	0	1	1

0=’control’; 1=’intervention’ - eGFR graph surveilence

### Approach to adaptations during the project

This is a quality improvement project and adaptations according to local need are expected. We recognise that there may be delays in securing agreement from participating sites, and difficulties with Information Technology. There are a number of different Laboratory Information Management Systems (LIMS) in use in the UK, and only one of these (“Telepath”) has currently been interfaced with the project software.

We will have a total of four steps, each of six months duration. In summer 2015 we performed an initial randomisation (using random number generation) to an intervention start-time. Due to delays and uncertainties with candidate sites, we performed a first randomisation to select the four centres in the first intervention step (from ten available at that time). A second randomisation to allocate the remaining 15 centres to the second, third and fourth randomisation steps was then performed in late 2015.

### Recruitment of renal centres

We have preferentially targeted renal centres: with good completeness of late presentation rate in existing UK Renal Registry data returns; that are served by a single laboratory or LIMS; and that have a high proportion of patients currently presenting late for RRT (as reported by the UK Renal Registry).

A predefined process for recruitment was followed, starting with email contact with renal centres and laboratories and following up with telephone conversations. Inclusion in the randomisation to allocate an intervention start time was performed once we had a formal expression of interest from both renal clinicians and laboratory scientists together with an indication from sites’ Information Technology departments that the technical requirements could be met.

Participating renal centres agree to: submission of vascular access data to the annual UK Renal Registry Multisite Dialysis Access Audit; submission of UK Renal Registry data in a timely fashion; and to provide the UKRR with the total number of new out-patient renal referrals (in-centre and outreach clinics) per month. The UK Renal Registry has Section 251 approval from the Health Research Authority to collect and hold identifiable information without individual patient consent, for patients with CKD stages 2–5, for audit and quality assurance purposes. The UKRR have permissions to hold patient-identifiable data and will hold the final dataset in a partnership agreement with Kidney Research UK. Access to the data will not be limited, except patient or centre identifiable information.

Laboratories will be required to either keep a log of all patients (containing individual level identifiers) for whom an eGFR graph is sent to the GP.

### Support for participating sites

The project grant includes the initial support necessary for laboratories to link their pathology systems to the SQL database and install the software. Training will be provided for local laboratory staff and staff costs for one year will be covered. The Heart of England Foundation Trust experience suggests the annual costs are in the order of £12,000 per year for a large laboratory serving a population of one million people. It is expected that the on-costs from year two onwards will be met locally. From the outset we have built in mechanisms to achieve sustainability, working with participating sites to develop business cases for local commissioners. The business case focuses on the savings derived from avoidance of dialysis being re-allocated to pay for the ongoing provision of eGFR graph surveillance. Experiences from HEFT suggest that delaying dialysis for one patient for one year will fund the graph surveillance for a population of 300,000 people for approximately 5 years.

### Outcome measures

Outcomes will be examined at renal centre level and, if necessary, laboratory level using Geographic Information Systems to map patients to laboratories. Routinely collected baseline data will be provided by the UK Renal Registry and baseline referral rates supplied by participating centres.

The UK Renal Registry (UKRR) routinely collects and publishes treatment and clinical performance data for all adult renal centres in the UK [10]. As part of this, it routinely receives an extract of data on numbers of patients starting dialysis in each renal centre and timeliness of referral.

Our primary quantitative outcome measure is the incidence of late presentation for renal replacement therapy, defined as any patient first seen by renal services within 90 days of starting renal replacement therapy. These data will aggregate into six-month time periods, two per calendar year (Jan to June; July to December).

The following secondary outcomes will be studied:(i.)the use of temporary vascular access for starting dialysis(ii.)latest eGFR measurement, within two weeks before start of RRT(iii.)mortality at 6 months from start of RRT in new RRT patients(iv.)the incident rate of ESKD, measured annually.

All outcomes measures are routinely collected by the UK Renal Registry with the exception of vascular access, which is collected annually as part of the Registry’s Multisite Dialysis Access Audit.

The number of new patient referrals (per quarter) will be recorded as a balancing measure. These data are readily extractable from renal centre appointment systems.

### Statistical analysis plan

#### Number of participants

We will present numbers of patients flagged to GPs by each laboratory, per time-period. We will present the number of patients referred to renal centres and number of new RRT patients, and these will be presented by renal centre per time-period. We will also provide a flow chart of the number of incident RRT patients that will be included in the analysis after excluding those with missing data.

#### Descriptive statistics

The characteristics of individuals by exposure (control versus intervention) will be presented for each renal centre.

#### Analysis of primary outcome

Analysis of changes in risk of late-referral will be performed using a mixed-effects logistic regression, as a patient level analysis, with the clustering at renal centres being accounted for by fitting renal centre as a random effect. The primary outcome response will be binary (patient referral <90 days = 1, patient referral ≥90 days = 0). It is expected that the risk of being late referred should decrease with the intervention. The odds ratio estimate of the risk of being late-referred for the treatment effect (intervention versus control) with 95% confidence interval will be presented (model 1). Analysis will be adjusted by time-period or step (model 2), and individual patients’ characteristics such as age at start of RRT, gender, primary renal diagnosis, ethnicity and deprivation score (model 3). Due to the nature of the intervention it is anticipated that its impact on late referral will change over time, as the risk of being late-referred is expected to decrease after the intervention is implemented, and possibly more so with time from start of intervention (we expect a cumulative effect, at least up to a certain point). Therefore we aim to explore for possible interaction between time and treatment effect (model 4).

The results from model 2 will be considered the primary result, as our intention is to determine if changes in the risk of being late-referred for RRT are related to the intervention and not to an independent time-trend.

Power calculations for the primary outcome have been derived on Stata [11], based on UKRR data returns from twelve candidate renal centres. The UKRR reached complete coverage of the UK in 2007 and data on adult incident RRT patients have been routinely collected since then. Therefore we are able to use data on new incident patients commencing RRT before the project started, and we plan to include in the analysis the population of RRT incident patients in 2013–14 for the participating centres. We therefore used the formula published by Woertman, which can accommodate the inclusion of additional historic data [12]. The percentage of late referral in these twelve centres ranged from 9 to 35%, with an average of 18%. With power set at 80%, alpha at 0.05 and intra-class correlation (ICC) at 0.05 (based on analysis of UKRR 2013 data) we should be able to detect a reduction in late presentation rate from 18 to 11%.

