Given the extreme financial constraints under which the UK National Health Service is currently operating, it is imperative to perform a robust evaluation of any quality improvement intervention. The proposed evaluation will ensure that the project is delivering improvement as expected and therefore represents an appropriate use of scant resource. It will also help to inform the aformentioned sites where the eGFR graph intervention is being introduced routinely outside the project [20].

The project has limitations and challenges. We recognise the complexities inherent in a stepped wedge approach, from both an analytical and operational perspective. The follow up is quite short and we do not have time to have a transition phase immediately following implementation of the intervention. We will not be performing interim analyses and believe that it is very unlikely that anything in these analyses would give good grounds to change the duration of the steps. However the number and duration of steps will be reviewed by a project Evaluation Advisory Board, if needed, as dictated by operational and logistical issues. There are several laboratory IT systems in operation across the UK and the need for the eGFR graph system to work across multiple platforms may impact upon the project time-lines. Delays will be mitigated by over-recruitment and pre-allocation of intervention start time at the point of formal expression of interest.

The UK pathology laboratory environment is evolving. The Audit Commission called for pathology services to be re-organised in 1993, but changes have been slow to be implemented. “Hub and spoke” models were recommended in Lord Carter’s 2008 review of pathology services, where routine (including GP) work is consolidated into large hubs. This model offers both opportunities and threats. Consolidation of high volumes of GP samples into a single laboratory/laboratory cluster will allow a single site deployment of our intervention to reach far larger numbers of surgeries. The risks are that historic pathology data may not be transferred to new systems, preventing the retrospective charting of renal function, and that there may be pathology reorganisations at participating sites within the project lifespan.

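### The primary model has no centre-by-period variance, so if centres drift differently over the ten half-years its 95% confidence interval will be too narrow

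*Protocol article*

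**What the plan says.** The protocol article, under *Analysis of primary outcome*, specifies a patient-level mixed-effects logistic regression with "the clustering at renal centres being accounted for by fitting renal centre as a random effect". No other random effect is named. Period enters as an adjustment: "Analysis will be adjusted by time-period or step (model 2"). The choice of primary analysis is explicit: "The results from model 2 will be considered the primary result". Model 4 is exploratory: "we aim to explore for possible interaction between time and treatment effect (model 4").

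Table 1 lays out ten six-month periods: four historical (2013–2014) and six in the core study (2015–2017). It shows 18 centres, A to R, in steps of 4, 5, 5 and 4. The text gives at least 19, with four randomised first and 15 later.

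The power statement reads "With power set at 80%, alpha at 0.05" and "intra-class correlation (ICC) at 0.05 (based on analysis of UKRR 2013 data"), and concludes that "we should be able to detect a reduction in late presentation rate from 18 to 11"%. Under *Analysis of secondary outcomes*, vascular access and six-month mortality are analysed like the primary outcome, and pre-RRT eGFR follows the same sequence of models.

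**The concern.** A single centre intercept treats two patients of one centre as equally correlated whether they start RRT in the same half-year or nearly five years apart. Common period effects remove the shared trend but not movement peculiar to one centre. In a stepped wedge, treatment status is fixed by centre and period. A departure of one centre from the common trend in some half-years therefore falls partly on the treatment contrast, while the model's standard error counts only patient-level noise within a centre and period.

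One year of registry data can give a within-year correlation. It cannot show that the correlation persists for five years. Model 4 does not help, because it lets the treatment effect change with time and adds no variance between centre-periods.

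At stake is the coverage of the primary interval, and of the intervals for the three secondary outcomes modelled the same way, in a project whose Discussion hopes to make the case for universal adoption.

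**Working it through.** **Inputs from the protocol.** Rates 18% and 11%; power 80%; alpha 0.05 (taken as two-sided, given the 95% interval); ICC ρ = 0.05; Table 1 layout.

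**Assumptions, not in the protocol.** Patients per centre-period n (20, 30, 31.5, 50), and the ratio r of between-period to within-period correlation (1, 0.9, 0.8). Variances are taken at the mean rate, p = 0.145.

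**1. The plan's own figure.** Individual randomisation of 18% against 11% needs 396 per arm, 792 in total. The stepped-wedge design effect for k = 4 steps, one measurement per step and b = 5 baseline periods is

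DE = [1 + ρ(kn + bn − 1)] / [1 + ρ(kn/2 + bn − 1)] × 3(1 − ρ) / [2(k − 1/k)].

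At n = 21 this is (10.4 / 8.3) × (2.85 / 7.5) = 0.476. Then 792 × 0.476 / 21 ≈ 18 centres. So 80% power needs about 21 patients per centre-period with 18 centres, 20 with 19, or 32 with 12. The stated figure is plausible, but it cannot be strictly reproduced because n is not given.

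**2. Standard error when centre deviations vary by period.** Let σ² = 0.145 × 0.855 = 0.124. The covariance of one centre's ten period means is (J = matrix of ones, I = identity):

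- model 2: ρσ² J + [(1 − ρ)σ²/n] I
- truth with ratio r: rρσ² J + [(1 − r)ρσ² + (1 − ρ)σ²/n] I

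The random-intercept generalised least squares estimator with period effects was evaluated on Table 1 (18 centres). Its true (sandwich) variance was divided by its model-based variance. R is the square root of that ratio, and type I error = 2Φ(−1.96/R).

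| n | R, r = 0.9 | type I | R, r = 0.8 | type I |
|---|---|---|---|---|
| 20 | 1.05 | 6.2% | 1.10 | 7.4% |
| 30 | 1.08 | 6.8% | 1.15 | 8.7% |
| 50 | 1.12 | 8.1% | 1.23 | 11.2% |

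At r = 1, R = 1 and type I error is 5.0%. A hand check is R ≈ √[1 + nρ(1 − r)/(1 − ρ)]. For n = 30 and r = 0.8 this is √(1 + 0.3/0.95) = 1.147.

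**3. Check on the logistic model itself.** Null data were simulated and fitted with a random-intercept logistic model with period effects (Wald test, 2,500 runs per cell; Monte Carlo standard error near 5% is √(0.05 × 0.95/2500) ≈ 0.4 points).

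| n | r = 1 | r = 0.9 | r = 0.8 |
|---|---|---|---|
| 20 | 4.8% | 6.0% | 7.1% |
| 30 | 5.3% | 7.1% | 8.2% |
| 50 | 5.4% | 8.4% | 11.8% |

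**4. Price of the correct model.** The 80%-power difference is (1.96 + 0.84) × SE, with the centre-by-period variance included, 19 centres (4, 5, 5, 5) and a normal reference.

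| n | r = 1 | r = 0.9 | r = 0.8 |
|---|---|---|---|
| 31.5 | 2.80 × 0.0199 = 5.6 points | 2.80 × 0.0214 = 6.0 | 2.80 × 0.0229 = 6.4 |
| 20 | 2.80 × 0.0249 = 7.0 points | 2.80 × 0.0261 = 7.3 | 2.80 × 0.0272 = 7.6 |

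With Table 1's 18 centres and n = 20, power for 18% to 11% goes from 77% (r = 1) to about 73% (0.9) and 70% (0.8).

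**The case against.** Four stronger readings are tempting, and the protocol supports none of them.

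- **That the model holds each centre's late-presentation rate constant.** It does not. Model 2 has period effects, so every centre's level moves with the common trend. Only the deviation from that trend is fixed.
- **That type I error is certain to exceed 5%.** The inflation depends on r being below 1, and the protocol gives no figure for r. A one-year ICC shows neither persistence nor decay.
- **That the protocol itself predicts centre-specific drift.** The Discussion says only that "there may be pathology reorganisations at participating sites within the project lifespan". The harm it links to changes in pathology services is the loss of historic results needed for charting, which concerns delivery of the intervention. The local adaptations it expects bear mainly on how the treatment effect varies between sites. Its caution about registry data concerns uniformity across sites, not change over time. These remarks make drift conceivable; they are not evidence of it.
- **That 18 or 19 centres make the test anti-conservative by themselves.** At r = 1 the main simulations gave 4.8–5.4%. Smaller runs of 1,500 gave 6.0–6.4%. Neither shows material inflation, and a degrees-of-freedom rule is a detail an article may leave to a full analysis plan.

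It is also fair to say that at about 20 patients per cell, roughly what the stated power implies for 18–19 centres, the inflation is modest.

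What survives is the model choice. The article names the random effect and declares which model is primary, so this is not detail lost in condensation. The only correlation figure offered does not bear on stability over five years.

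**Conclusion.** The point holds in conditional form. The primary model leaves centre-by-period variation unmodelled over ten half-years. If such variation exists, the primary interval is too narrow: type I error is about 6–7% at 20 patients per centre-period, 7–9% at 30 and 8–11% at 50, for ratios of 0.9 to 0.8, and about nominal at a ratio of 1. These sizes rest on the stated ICC of 0.05, on Table 1, and on assumed values for the ratio and the cell size. The change should be made before analysis, because it is simple and protects the main result.

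**What to change.** Add a random effect for centre-by-period, alongside the centre effect, to the mixed models for late presentation, vascular access, pre-RRT eGFR and six-month mortality. Restate the detectable difference over a range of correlation ratios and patients per centre-period, and state the cell size used. The historical registry data could inform the ratio.

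The change needs one more variance component and no new data. If the extra variance is nil, the term should estimate near zero and little is lost. Otherwise the interval widens, and at about 20 patients per cell the 80%-power difference passes the stated 7 points (18 − 11), so the power claim may have to be relaxed.

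A small-sample reference distribution is optional. It has its own price: with a t reference on 17 degrees of freedom and 19 centres, the difference at ratios 0.9/0.8 becomes 6.4/6.8 points at 31.5 per cell and 7.8/8.1 at 20.
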